##### Secondary outcomes

2.4.2.2

The Clinical Global Impressions Scale, Improvement (CGI-I) (53) (blinded interview; 0, 3, 6, and 12 months) will assess primary caregiver impressions of improvement/worsening of EBP, ranging from complete absence of EBP (1) to “disastrously worse” (7). Children will be classified as “responders” for analytic and descriptive purposes if they demonstrated a 25% decrease on the irritability scale and a CGI-I score of 1 or 2.

Caregiver well-being will be assessed by measuring caregiver depression, caregiver anxiety, and parenting stress (parent self-report; 0, 3, 6, 9, and 12 months) Depression will be measured through the Center for Epidemiological Studies Depression Scale-Revised (CESD-R) (54), a 20-item scale with strong psychometric properties.

Caregiver anxiety will be measured using the brief Generalized Anxiety Disorder-7 (GAD-7) (55); and parenting stress will be assessed using a brief version of the Parenting Daily Hassles (56) and the Autism Parenting Stress Index (57).

Specific parenting behaviors will be measured using the Parenting Young Children (PARYC) (58) and Positive Affect Index (59) (parent self-report; 0, 6, and 12 months). The Parental Monitoring Scale (PMS) (60) will also be administered for older children [parent and youth (11+) self-report; 0, 6, and 12 months).

Parenting self-efficacy and coping will be measured using the Parent Empowerment and Efficacy Measure (PEEM) (61) and the Brief COPE (62) (parent self-report; 0, 6, and 12 months). Caregiver thoughts and feelings about their child, and their relationship with their child, will be audio-recorded and coded by assessors blinded to intervention status, using the Autism-Specific 5-Minute Speech Sample (blinded coders; 0, 6, and 12 months) (63). Observed parenting behavior will be coded by blinded observers using a modified version of the Coder Impressions Inventory (COIMP) (64).

Connectedness to and use of services will be measured at 0, 6, and 12 months using a modified version of the Service Utilization Questionnaire developed for a previous Canadian Family Check-Up study.

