#### Sample and recruitment

2.1.3

The study sample consists of 80 children/youth with ASD and high levels of EBP and their caregiver(s).

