##### Inclusion criteria

2.1.3.1

Child 6–17 years of age.Confirmed diagnosis of ASD.Enrollment in the Ontario Autism Program (OAP).Minimum developmental age of 2 years.Elevated EBP as determined by high or very high scores on the emotional problems (≥ 5), hyperactivity (≥ 8), and/or conduct problems (≥ 4) scales of the Strengths and Difficulties Questionnaire (SDQ) (37) OR a score ≥ 12 on the irritability subscale of the Aberrant Behavior Checklist (ABC) (38).Residing with the same caregiver for at least 5 days/week OR every other week for the past 2 months and the foreseeable future.

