#### Screening measures

2.4.1

Families will be asked for basic demographic information to determine eligibility (e.g., child date of birth, child’s primary residence and caregivers). To determine if child has a developmental age of at least 2 years, caregivers will be administered item #41 from the Autism Diagnostic Interview (ADI-R) which assesses how well the child uses language to communicate. They will also be asked whether the child can follow simple two-step commands and if they use any alternative communication devices. In addition, caregivers will be asked questions about the presence or absence of intellectual and learning disabilities.

Child EBP will be assessed as follows:

The *Strengths and Difficulties Questionnaire (SDQ)* (45), a widely used 25-item behavioral screening questionnaire for children ages 2–17 years. The Prosocial Behavior scale showcases strengths, while the remaining four evaluate negative behaviors such as emotional symptoms, conduct problems, hyperactivity/inattention, and peer relationship problems. Satisfactory psychometric properties have been reported (45) and scores from the SDQ and the CBCL have been shown to be highly correlated (48). A child is eligible if the conduct score ≥ 4 OR the hyperactivity score is ≥8 OR the emotional problems score is ≥5.

The irritability subscale of the *Aberrant Behavior Checklist (ABC)* (50), a commonly used measure of child EBP in psychosocial and pharmacological RCTs in autism research. Because we aim to recruit children with elevated irritability, participants were included if the ABC irritability score is ≥12 as per norms developed for autistic children and youth (38).

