##### Primary outcome

2.4.2.1

Child emotional dysregulation will be measured using the Aberrant Behavior Checklist (ABC) Irritability subscale (51) and the Home Situations Questionnaire—Autism Spectrum Disorder (HSQ-ASD; parent report; 0, 3, 6, 9, and 12 months) (52).

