#### Effectiveness—aim #1

2.5.1

Analyses will be conducted following an intent-to-treat approach. Two-wave latent difference score models will be used to evaluate whether participation in the FCU®, compared to TAU, is associated with greater decreases in child EBP (primary outcome) and caregiver depression and parenting stress from baseline to 6 and 12 months post-baseline, and greater increases in positive parenting from baseline to 6 and 12 months post-baseline. A sensitivity power analysis indicates that an *N* = 80 is powered to detect a significant regression coefficient equivalent to Cohen’s *d* = 0.56, α ≤ 0.05 (one-tailed), which is aligned with systematic reviews noting moderate (~*d* = 0.60) effect sizes for parenting programs among caregivers of autistic children (19, 20). A one-tailed test was chosen based on our directional hypotheses and the wealth of evidence supporting the effectiveness of the FCU®. Given that *d* = 0.56 is somewhat larger than that found in previous studies of the FCU® in non-autistic children, we will also conduct two additional sets of analyses. First, we will calculate a Bayes Factor for each analysis to determine whether the pattern of effects are more consistent with the null (the two groups do not differ) or alternative hypotheses (the two groups differ). Second, we will conduct exploratory, descriptive analyses to determine the percentage of participants in each condition defined *a priori* as responders using the ABC and CGI, and describe intervention-, organization and policy-relevant child, family and intervention characteristics in each group.

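### The 25% irritability responder rule has no baseline minimum, although children can enter on SDQ scores with little or no irritability

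*Protocol article*

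**What the plan says.** **Entry.** Section 2.1.3.1 (Inclusion criteria) accepts "high or very high scores on the emotional problems (≥ 5), hyperactivity (≥ 8), and/or conduct problems (≥ 4) scales" of the SDQ, "OR a score ≥ 12 on the irritability subscale of the Aberrant Behavior Checklist (ABC"). A child who qualifies on the SDQ needs no minimum irritability score.

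**Stated intent.** Section 2.4.1 (Screening measures) gives the SDQ thresholds and then says of the ABC: "Because we aim to recruit children with elevated irritability, participants were included if the ABC irritability score is ≥12". The word OR is not repeated there.

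**Primary outcome.** Section 2.4.2.1 names two scales: "Child emotional dysregulation will be measured using the Aberrant Behavior Checklist (ABC) Irritability subscale (51) and the Home Situations Questionnaire" for autism (HSQ-ASD).

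**Responder rule.** Section 2.4.2.2 classes children as responders "if they demonstrated a 25% decrease on the irritability scale and a CGI-I score of 1 or 2". The CGI-I comes from a blinded interview and "will assess primary caregiver impressions of improvement/worsening of EBP", so it covers emotional and behaviour problems generally, not irritability alone. No minimum baseline, minimum absolute fall or rule for a zero baseline accompanies the 25%.

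**Use.** Section 2.5.1 says "we will conduct exploratory, descriptive analyses to determine the percentage of participants in each condition defined" in advance as responders. Section 2.1.1, item (d), compares FCU responders with non-responders.

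**The concern.** The entry rule and the responder rule look at different things. A child can be admitted for emotional symptoms or hyperactivity with an irritability score near zero, and is then judged partly on whether irritability falls by a quarter.

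Near the floor, a relative criterion fails in two directions:

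- **Too easy.** At a low baseline, a one-point fluctuation satisfies it.
- **Too hard, or impossible.** A child who really improves in the problem that brought them in, and earns a CGI-I of 1 or 2, is a non-responder if a low irritability score happens not to drop. At a baseline of zero the percentage cannot be computed.

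At stake are the responder percentages by arm and the description of how responders differ from non-responders, which the plan intends to use for refining the programme. For one of the two primary scales there is a secondary worry: children at the floor of ABC Irritability cannot show benefit on it.

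**Working it through.** **1. The plan's own figure.** Inputs from section 2.5.1: N = 80, one-tailed alpha 0.05, detectable d = 0.56. Power and allocation are not stated; 80% and 40 per arm are assumed.

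Detectable d = (1.645 + 0.842) × √(2/40) = 0.556. One-tailed power at d = 0.56 with 40 per arm is 0.799 (noncentral t). The stated 0.56 reproduces.

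**2. Points needed for a 25% fall.** Assuming whole-point scoring, the minimum drop is 0.25 × baseline, rounded up:

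| Baseline | Drop needed |
|---|---|
| 0 | undefined |
| 4 | 1 |
| 8 | 2 |
| 12 | 3 |
| 24 | 6 |

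**3. Chance of meeting the irritability half with no true change.** P = Φ((−drop + 0.5)/SD), where SD is the SD of change. The protocol gives no SD; 3 to 7 points is assumed.

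| Baseline | SD 3 | SD 7 |
|---|---|---|
| 4 | Φ(−0.167) = 43% | Φ(−0.071) = 47% |
| 12 | Φ(−0.833) = 20% | Φ(−0.357) = 36% |
| 24 | Φ(−1.833) = 3% | Φ(−0.786) = 22% |

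A simulation with whole-point scores floored at 0 and an assumed measurement error of 2 points (change SD 2 × √2 = 2.8) gives 43% at 4, 19% at 12 and 6% at 20. If error is instead proportional to the score (20% coefficient of variation, assumed), the gradient is much flatter: 33% at 4, 23% at 12, 21% at 20.

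**4. Adding the CGI-I condition.** Suppose CGI-I 1-2 is met by 10-30% of children, independently of the ABC (both assumed). With the 2-point error:

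- baseline 4: 0.43 × 0.10 to 0.43 × 0.30 = 4-13%
- baseline 12: 0.187 × 0.10 to 0.187 × 0.30 = 2-6%
- baseline 20: 0.056 × 0.10 to 0.056 × 0.30 = 0.6-1.7%

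Joint false response is much lower than in step 3 but still depends on baseline.

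**5. The opposite error.** Take a child at baseline 4 who truly improves elsewhere, has CGI-I 1 or 2, and has no true change in irritability. Step 3 gives a 43-47% chance of the responder label and so 53-57% of the non-responder label. The label is close to a coin toss. At baseline 0 it cannot be assigned by the rule.

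**6. Dilution of ABC Irritability, illustration only.** Let f be the share of children with no scope to improve on this scale. Assume zero effect in them and 0.56 in the others, so d = 0.56 × (1 − f).

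| f | d | One-tailed power, 40 per arm |
|---|---|---|
| 0 | 0.56 | 80% |
| 20% | 0.45 | 63% |
| 30% | 0.39 | 54% |

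The protocol gives no value for f.

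**The case against.** Several points on the other side are sound and limit the finding.

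- **Low scorers do not become responders through irritability noise alone.** A reader might infer this from the 43-47%, but that figure covers half of the rule. A CGI-I of 1 or 2 from a blinded interview is also required. This stands. What it does not do is protect the child who passes the CGI-I and is then sorted by drift.
- **The responder work is exploratory and descriptive.** This stands: no primary inference rests on it.
- **A reader might infer that the primary effect is diluted and the trial underpowered.** The documents do not support that. The share entering with low irritability is not given, the SDQ and ABC routes may overlap heavily, and a child scoring 8 to 11 has room to fall. The 0.56 is a detectable effect for the whole sample of 80, not an effect stated for irritable children. HSQ-ASD is also primary, and its floor cannot be judged from the article.
- **A reader might infer that the emotional and hyperactivity problems are never assessed again.** This is not shown either. The CGI-I rates these problems overall, and the condensed article refers to exploratory measures that it does not list.
- **Broad entry was deliberate.** Section 1.4 says so. Section 2.4.1 can also be read as listing each instrument's threshold in turn, which fits OR. The clause about aiming for elevated irritability still sits badly with the entry rule.
- **Handling of very low baselines could be left to an analysis plan.** That is fair for fine detail. But the article fixes the rule for every child, and followed as written it has no value at a baseline of zero.

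**Conclusion.** The point holds in limited form. The relative 25% criterion is badly fixed for a sample that can include children with little or no irritability: it turns on 1 point at a baseline of 4 and is undefined at 0. The resulting misclassification runs both ways and affects the responder percentages and the responder/non-responder comparison, not the primary test.

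The 43-47% rests on an assumed change SD of 3 to 7 points, and the steep gradient weakens if error grows with the score. The joint rates rest on assumed CGI-I frequencies and on independence. How many children are affected is unknown, so the dilution figures show sensitivity only and apply to ABC Irritability alone. The change is worth making because it alters a result the trial will report and uses data already collected.

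**What to change.** 1. Compute the responder rate (25% fall plus CGI-I 1 or 2) only in children with baseline ABC Irritability of at least 12, the trial's own cut-off, where the criterion needs at least 3 points. State that the 0-month score defines the subset.
2. Report CGI-I 1-2 for the remaining children separately, by arm, without pooling them into the responder percentage. Counting them as responders on CGI-I alone would loosen the rule for the group at issue: on the assumptions above, from 4-13% to 10-30% at baseline 4.
3. Pre-specify the ABC Irritability comparison in the same subset as a supportive analysis.
4. Reconcile the recruitment aim in section 2.4.1 with the OR rule in section 2.1.3.1.

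No extra measures are needed. Repeating the SDQ at follow-up is not proposed, since families asked for a shorter battery (section 1.2). The cost is a smaller denominator for the responder rate and one more low-powered supportive analysis; recruitment is unaffected.

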##### Baseline covariates, mediators, and moderators

2.4.2.3

Child cognitive skills will be measured using the *Stanford-Binet Intelligence Scales, 5th* Edition routing version (65), which can be administered to people ages 2–85 years. The routing version assesses nonverbal fluid reasoning and verbal knowledge and takes about 15 min to administer. Because the FCU® was developed for families with children ages 2–17 years, it was determined that children taking part in the study must have a minimum developmental age of 2 years. Interested families are asked questions during screening to get a sense of their child’s developmental age, which is measured more formally through the Stanford-Binet at the baseline visit. If this testing determines that a child is developmentally below the age of 2, families will not be able to continue in the study. In this case, they will be provided the gift cards for the baseline visit and connected to a Family Service Coordinator in the Autism Program for other program options.

Child language will be measured using the *Oral and Written Language Scales-II (OWLS-II)* (66), a widely used receptive and expressive language assessment suitable for children with ASD. The OWLS-II takes approximately 20 min to administer.

Child autistic symptoms will be measured at baseline using the Social Communication Scale—Current (SCQ-C) (67). Child sleep will be assessed through two questions from the *2014 Ontario Child Health Study (OCHS) Selected Child and Adolescent Psychiatric Interview (CAPI)* (68, 69) that assess child’s average number of hours of sleep and perception of quality of sleep as well as the parent-report *Children’s Sleep Hygiene Scale* (70). Youth participating in the study will complete the self-report *Adolescent Sleep Hygiene Scale* (71).

Caregiver executive function will be measured using the *Executive Skills Questionnaire—Revised (ESQ-R)* at baseline only (72). Caregiver emotional regulation will be measured through the *Difficulties in Emotional Regulation Scale—Short Form (DERS-SF)* (73), an 18-item scale that assesses deficits in regulating emotions.

Parent sleep will be assessed using the Sleep Hygiene Index (74), a 13-item measure that assesses behaviors thought to compromise sleep hygiene. It has good internal consistency, test–retest reliability, and is positively correlated with other sleep measures. Parents will also be asked the average number of hours of sleep they get each night and to rate the quality of their sleep (very good, fairly good, fairly bad, and very bad).

Household chaos will be measured through the *Confusion, Hubbub and Order Scale (CHAOS)* (75), which is a 15-item measure of environmental confusion. Caregiver alcohol use will be assessed through the three-question *Alcohol Use Disorders Identification Test—Consumption* (76) which assesses the potential harmfulness of a person’s alcohol consumption. Caregiver drug use will be assessed using the *Drug Abuse Screening Test (DAST-10*) (77), which has moderate to high levels of reliability and validity.

#### Implementation measures

2.4.3

##### Quantitative data

2.4.3.1

Clinical costs will be tracked, including training, clinician hours, supervisor hours, travel, equipment, and administrative costs.

Organizational and clinician readiness for change will be collected from staff, leadership, and clinicians (0, 6, and 12 months) using the *Evidence-Based Practice Attitudes Scale* (78), *Organizational Readiness for Implementing Change* (79), *Acceptability of Intervention Measure* (79), *Feasibility of Intervention Measure* (79), *Intervention Appropriateness Measure* (79), and the *Oldenburg Burnout Inventory* (80).

The *Working Alliance Inventory-Short Revised* (81, 82) is a measure of the therapeutic alliance between a therapist and their client. Is it brief (client version 12 questions, therapist version 10 questions) and has good psychometric properties. It will be administered after the Get to Know You Visit, feedback session, and third and sixth sessions of EDP (if applicable).

Satisfaction with the intervention will be measured by the *FCU® Satisfaction Scale* (administered to caregivers post-FCU®) (48). In addition, “dosage” (the number of FCU® sessions attended by each family) will be tracked.

With written consent from families, clinicians will videorecord their FCU®/EDP sessions to be able to evaluate fidelity to the model. Fidelity will be assessed by the *COACH Fidelity Rating* (83) system created by FCU® developers to assess adherence to key FCU®/EDP components on a 1–9 scale. During each 6-month period of the study, four videotaped sessions/clinician will be randomly drawn to assess average levels of fidelity in early, middle, and sustainability phases.

##### Qualitative data

2.4.3.2

See Figure 3. The qualitative component of the implementation study will follow the principles of qualitative description, which is an applied qualitative health research methodology commonly used alongside intervention evaluations. It is well suited to addressing the implementation aims of the present work via its pragmatic emphasis on generating a rich description of the phenomenon of interest by using and staying interpretively close to the words of participants (84, 85). To this end, clinicians and family service coordination staff will be purposefully sampled and invited to join focus groups aimed at understanding contextual barriers and facilitators to FCU® implementation (*N* ~ 10–15; 0, 6, and 18 months). The perspective of leadership will be obtained through individual interviews (*N* ~ 5; 0 and 18 months). Transcribed, coded themes will be fed back iteratively for clinical quality improvement purposes, protecting confidentiality.

**Figure 3 fig3:**
[figure not shown]
Study flow, implementation design. FCU^®^, Family Check-Up; EDP, Everyday parenting curriculum. ^*^Caregivers and consenting youth invited to qualitative interviews after completing 12-month visit.

Open-ended questions about experience with the FCU® and/or study will be included in 12-month participant questionnaires. In addition, all consenting caregivers and youth (who are capable of consenting) in the FCU® arm will be invited to participate in individual qualitative interviews asking about their experience of family, parenting, and child change vs. stability throughout the intervention, acceptability of the FCU® in this service setting and facilitators/barriers to engagement. When possible, we will briefly interview FCU®-arm participants classified as “non-engagers” (i.e., did not complete the feedback session) about barriers to engagement after their 12-month visits throughout the study.

### Analyses

2.5

#### Effectiveness—aim #1

2.5.1

Analyses will be conducted following an intent-to-treat approach. Two-wave latent difference score models will be used to evaluate whether participation in the FCU®, compared to TAU, is associated with greater decreases in child EBP (primary outcome) and caregiver depression and parenting stress from baseline to 6 and 12 months post-baseline, and greater increases in positive parenting from baseline to 6 and 12 months post-baseline. A sensitivity power analysis indicates that an *N* = 80 is powered to detect a significant regression coefficient equivalent to Cohen’s *d* = 0.56, α ≤ 0.05 (one-tailed), which is aligned with systematic reviews noting moderate (~*d* = 0.60) effect sizes for parenting programs among caregivers of autistic children (19, 20). A one-tailed test was chosen based on our directional hypotheses and the wealth of evidence supporting the effectiveness of the FCU®. Given that *d* = 0.56 is somewhat larger than that found in previous studies of the FCU® in non-autistic children, we will also conduct two additional sets of analyses. First, we will calculate a Bayes Factor for each analysis to determine whether the pattern of effects are more consistent with the null (the two groups do not differ) or alternative hypotheses (the two groups differ). Second, we will conduct exploratory, descriptive analyses to determine the percentage of participants in each condition defined *a priori* as responders using the ABC and CGI, and describe intervention-, organization and policy-relevant child, family and intervention characteristics in each group.

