### Study design

2.1

The step-wise progression of evidence-based practice from efficacy to effectiveness research, and then to eventual implementation into community practice, has traditionally encompassed a lengthy undertaking that has often resulted in poor intervention effects in real-world settings (24, 25). An implementation science approach seeks to shorten this research-practice gap by considering and evaluating outcomes that genuinely reflect real-world settings and concerns (24, 25). We will employ a Type 1 hybrid implementation-effectiveness approach studying the FCU®. This entails evaluating the program’s effects on the emotional well-being and functioning of autistic children and their caregivers (e.g., parents) as delivered by autism therapists trained in the FCU® model using a proof-of-principle randomized controlled trial (RCT) design, integrated with a mixed methods study focused on concurrently and explicitly evaluating facilitators and barriers to the implementation of the clinical intervention within an autism service setting (33). This design is particularly relevant when there is strong face validity for implementing an intervention in a new setting and/or population, indirect evidence of efficacy (e.g., evidence in other populations), and strong impetus to effect systems-level change.

The current study therefore includes two blended components:

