#### Effectiveness

2.1.1

The effectiveness study design is a parallel-group effectiveness randomized controlled trial (RCT) within an Autism Service located within a regional tertiary healthcare center serving a large city and surrounding small-urban and rural areas in Ontario, Canada. A sample of 80 children aged 6–17 years who are functionally speaking (or, “functionally verbal”) with clinically confirmed diagnoses of ASD and high levels of EBP and their families will be enrolled and randomized into either the FCU® or treatment as usual (TAU) with outcome assessments at 0, 3, 6, 9, and 12 months.

We will estimate the effectiveness of participation in the FCU® (+ up to 6 months of optional EDP sessions) vs. Treatment as Usual (TAU) by families of autistic children and youth aged 6–17 years in (a) decreasing child EBP (primary outcome), (b) decreasing caregiver depression, parenting stress, and (c) increasing positive parenting practice. (d) We will describe qualitative and quantitative differences in child and caregiver outcomes and connectedness to child and family services between intervention arms, and between FCU® participants classified as responders vs. non-responders.

Primary and secondary outcomes will be measured at 6 months, with follow-up visits at 9 and 12 months to determine if these effects fade out or are sustained.

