#### Randomization and blinding

2.1.5

Randomization will occur following the baseline visit to reduce risk of differential attrition. Participants will be randomly assigned to one of two conditions (FCU® or Treatment as Usual) using an internet-based randomization service; https://www.randomize.net/. Randomization will be stratified by child chronological age (6–10 and 11–17 years) and by presence/absence of co-occurring intellectual disability. Participants will be informed of their treatment arm status by the Research Coordinator or another research staff member who will not conduct any follow-up measures.

Participants will be informed of their right to withdraw from the study at any time. Furthermore, the lead principal investigator (LPI) may decide to withdraw a participating family from the study, if required, to mitigate undue risk to caregiver, child, research staff, or FCU® clinician.

Study participants will be withdrawn from the study under the following conditions:

If it is determined that the caregiver or child has an acute psychiatric crisis (e.g., psychosis) that will interfere with the ability to participate in the study.If a caregiver is experiencing an extreme crisis (e.g., related to an abusive or violent relationship) that interferes with the ability to participate in the study.If caregiver, child, research staff, or FCU® clinician experience an adverse event that is deemed by the LPI be an unacceptable safety risk.Death of child or participating caregiver.If participant behaviors or circumstances are deemed to unduly compromise the safety of the treating clinician or research staff (e.g., violence or unsafe behaviors toward research staff or clinician; unsafe conditions in home).If the LPI deems it is in the participants’ best interest to discontinue the study treatment.Loss of custodial caregiver status, if consent not obtained from replacing custodial caregiver (e.g., other caregiver, child protection service).

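### The stated detectable effect of d = 0.56 appears to make no allowance for FCU families sharing clinicians, and no clinician term is named in the analysis model.

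*Protocol article*

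**What the plan says.** Section 2.1.1 of the protocol article plans "A sample of 80 children aged 6–17 years who are functionally speaking" and their families. Section 2.1.5 randomizes family by family: "Participants will be randomly assigned to one of two conditions (FCU® or Treatment as Usual"). It adds that "Randomization will be stratified by child chronological age (6–10 and 11–17 years) and by presence/absence of co-occurring intellectual disability". Clinician is not a stratification factor.

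The programme is tested "as delivered by autism therapists trained in the FCU® model" (section 2.1). Section 2.3.2 has a clinician conduct every FCU visit. Section 2.2.3 adds optional individual parenting sessions, weekly to biweekly, for at most 6 months. Section 2.4.3.1 draws recorded sessions by clinician: "four videotaped sessions/clinician will be randomly drawn to assess average levels of fidelity". Usual-care families are connected to a service coordinator (section 2.3.1) and have no FCU clinician during the trial.

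Section 2.5.1 names the model ("Two-wave latent difference score models will be used to evaluate whether participation in the FCU®, compared to TAU") and says that the sample "is powered to detect a significant regression coefficient equivalent to" a Cohen's d of "0.56, α ≤ 0.05 (one-tailed"). It gives no power level, allocation ratio, number of clinicians, ICC or design effect. It neither includes nor rules out a clinician term.

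**The concern.** About 40 individually randomized families receive the FCU from a smaller set of clinicians, while the comparison arm has no such grouping. This is a partially nested design. If clinicians differ in the results they obtain, outcomes of families with the same clinician are positively correlated and the variance of the FCU mean is larger than under independence.

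An analysis that ignored this would give intervals that are too narrow and a one-sided test that rejects too often. A detectable effect computed without it would look better than it is. The margin is thin by the article's own benchmark: section 2.5.1 sets 0.56 against literature effects of about 0.60, a gap of 0.04, and concedes that 0.56 is already somewhat larger than earlier FCU studies found. Section 3.6 ties the next step to whether significant effects are shown, so it also matters whether an effect belongs to the programme or to one or two clinicians.

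**Working it through.** **Inputs from the article.** N = 80 (section 2.1.1); d = 0.56 and one-sided alpha 0.05 (section 2.5.1).

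**Assumptions.** 80% power; 1:1 allocation (40 per arm); 3 to 10 FCU clinicians with equal caseloads; ICC 0.02, 0.05 or 0.10; clustering in the FCU arm only. The one rough guide to the number of clinicians is in section 2.4.3.2, where focus groups total about 10 to 15 people, clinicians and coordination staff combined. That is a purposive sample and not a limit.

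**Step 1: reproduce 0.56.** Normal approximation: d = (1.645 + 0.842) × sqrt(2/40) = 0.556. With the noncentral t distribution, d = 0.561, and power at d = 0.56 is 0.799. Two variants do not match: two-sided 5% with 80% power gives 0.634, and one-sided 5% with 90% power gives 0.660 (both t). The published figure is therefore what a simple comparison of independent families gives.

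**Step 2: add clustering in the FCU arm.** With k clinicians, caseload m = 40/k.
- FCU-arm design effect: DE = 1 + (m − 1) × ICC
- Variance factor for the arm difference: f = (DE + 1)/2
- Detectable d = 0.561 × sqrt(f)
- True one-sided error of an unadjusted test = 1 − Φ(1.645/sqrt(f))
- Power at 0.56 = Φ(0.56/(0.2236 × sqrt(f)) − 1.645), where 0.2236 = sqrt(2/40)

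Example, k = 5 and ICC 0.05: m = 8; DE = 1 + 7 × 0.05 = 1.35; f = 1.175; sqrt(f) = 1.084; d = 0.61; error 6.5%; power 75%.

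| Clinicians | ICC | DE | Detectable d | One-sided error | Power at 0.56 |
|---|---|---|---|---|---|
| 10 | 0.02 | 1.06 | 0.57 | 5.3% | 79% |
| 10 | 0.05 | 1.15 | 0.58 | 5.6% | 78% |
| 10 | 0.10 | 1.30 | 0.60 | 6.3% | 76% |
| 5 | 0.02 | 1.14 | 0.58 | 5.6% | 78% |
| 5 | 0.05 | 1.35 | 0.61 | 6.5% | 75% |
| 5 | 0.10 | 1.70 | 0.65 | 7.8% | 70% |
| 3 | 0.02 | 1.25 | 0.59 | 6.0% | 76% |
| 3 | 0.05 | 1.62 | 0.64 | 7.5% | 71% |
| 3 | 0.10 | 2.23 | 0.71 | 9.8% | 63% |

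**Step 3: the ends of the range.** With 8 to 10 clinicians and ICC 0.01 to 0.02, the detectable d is about 0.57, a negligible change. An analysis that does estimate the clinician variance also loses degrees of freedom: with 4 clinicians and ICC 0.05 (DE 1.45, about 8 degrees of freedom) the detectable d is about 0.67, against 0.62 from the formula above.

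**The case against.** A reader might infer that the planned model treats all 80 families as independent and that its standard error is therefore wrong. The article does not support this. It names a class of model and is silent on clinician terms and on how the variance is estimated, which a condensed article may leave to a full protocol or analysis plan that is not shown. The sharing of FCU clinicians also concerns about 40 families, not 80. What remains is that the printed 0.56 equals the independence figure, and an adjustment specified elsewhere would not change that.

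A reader might also infer from the fidelity sampling that the investigators expect clinicians to differ. The stated purpose is to follow average fidelity across early, middle and sustainability phases, so it shows that clinicians hold repeated sessions and says nothing about the ICC for child outcomes. Contact may also be short: the core is an interview and a feedback visit, the parenting sessions are optional, and research staff conduct the baseline assessment.

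Nor is 40 versus 40 independent families the only route to 0.56. Section 2.5.1 refers to a regression coefficient. If change is regressed on baseline with a correlation of 0.39, then for 5 clinicians and ICC 0.05 the result is 0.561 × sqrt(1.175 × (1 − 0.39²)) = 0.56, so the gain cancels the loss. Nothing in the article says that such a gain was counted, but the figures above are before any gain of this kind.

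Finally, if inference is meant only for these particular clinicians, treating them as fixed is defensible and the error rate is not inflated in the way shown. That sits less easily with the article's stated interest in scale-up.

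**Conclusion.** The point holds in a limited form. The published d = 0.56 matches a calculation with no clinician design effect, and the article names no clinician term. Whether this matters depends on two quantities that the article does not give. The effect is negligible with many clinicians and a small ICC. It is material with few clinicians and an ICC of 0.05 or more: at 5 or fewer clinicians the detectable effect then passes the article's own benchmark of about 0.60. The conclusion rests on the assumed 80% power and 1:1 allocation, a positive ICC, inference beyond the clinicians in the trial, and no counted gain from baseline. It is a reason to qualify the figure and add a check. It does not show that the primary analysis is invalid.

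**What to change.** Keep the primary model and make three changes:

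1. Link each FCU family to its treating clinician in the analysis data.
2. Pre-specify one partially nested sensitivity analysis, with a clinician effect in the FCU arm only and small-sample degrees of freedom. If that variance cannot be estimated, report the primary interval widened for ICC 0.02, 0.05 and 0.10, using the actual caseloads.
3. State beside 0.56 that it assumes no clinician clustering, give the number of clinicians, and show the range by clinician number and ICC (about 0.57 to 0.71 for 3 to 10 clinicians and ICC 0.02 to 0.10, before any baseline gain).

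The cost is one extra analysis, slightly wider sensitivity intervals and a less favourable stated figure. No extra families are needed.
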